### Primary outcome

Quality of life is evaluated multi-dimensionally using the Taiwan Chinese Version of the EORTC Quality of Life Questionnaire C30 (QLQ-C30). The patients will complete the questionnaire at baseline (first visit), two weeks later (second visit), four weeks later (third visit) and eight weeks later (fourth visit). The score will be calculated and compared within group and between groups before and after medication.

The laboratory data collected will be also used to evaluate the general health status and monitor the liver and renal functions to assess the safety of SMS.

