**Methods/design:**

In this study, inclusion criteria are postoperative patients with histologically confirmed cancer within 3 years who are undergoing chemotherapy or radiotherapy, more than 18 years old, have given signed informed consent, have the ability to read Chinese, and the ability for oral intake.

Exclusion criteria include being pregnant, breast feeding, having completed chemotherapy or radiotherapy, brain metastasis with Eastern Cooperative Oncology Group (ECOG) performance status of two to four, delusion or hallucinations, acute infection, and have received medications under other clinical trials.

The patients were separated into an intervention group (Shen-Mai-San, SMS) and a placebo group for four weeks using a randomized, double-blind procedure. The European Organization for Research and Treatment of Cancer (EORTC) Quality of Life questionnaire (QOL-C30) was used to evaluate the quality of life. General data, hemoglobin (Hb), hematocrit (Hct), glutamic-oxalacetic transaminase (GOT), glutamic-pyruvic transaminase (GPT), blood urea nitrogen (BUN), creatinine, carcinoembryonic antigen (CEA), TCM diagnosis data and heart rate variability (HRV) were also recorded. These data were collected at baseline, two weeks and four weeks after receiving medication. The patients were prescribed granules which contained therapeutic medicines or placebo. Paired-T test was used for statistical analysis.

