### Participants

Patients will be recruited from the outpatients of the Oncology and Chinese Medicine Department in ChangHua Christian Hospital, a medical center in central Taiwan. Sixty patients will be recruited for the study and divided into an intervention group and a placebo group.

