### Intervention

One experienced TCM physician will be assigned to record the general data, TCM diagnostic data and prescribed medication for two weeks at the first visit. The patients will take the prescription to the pharmacy and the CRC will give either SMS or placebo in a capsule containing either 0.5 mg medication or starch. Patients will take eight capsules three times a day. The intervention period will be four weeks. Two weeks and four weeks after the first visit, patients will come back to out-patient-department (OPD) for clinical evaluation and medication.

After four weeks on the prescribed medication, the patients will stop taking SMS and placebo for another four weeks and then come back to OPD for clinical evaluation.

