### Statistical analysis

Statistical analysis will be performed by the Department of Mathematics and the Institute of Statistics and Information Science, National Changhua University of Education in Taiwan. We will use the statistical software R to analyze the data. Paired-T test will be derived for statistically analysis.

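### The primary outcome names no deciding QLQ-C30 score, visit or contrast, so a 5% false-positive rate is not held even if a single score is meant

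*Protocol article*

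**What the plan says.** The Primary outcome section of the protocol article defines the outcome through one instrument: "Quality of life is evaluated multi-dimensionally using the Taiwan Chinese Version of the EORTC Quality of Life Questionnaire C30 (QLQ-C30". It is completed "at baseline (first visit), two weeks later (second visit), four weeks later (third visit) and eight weeks later (fourth visit", which makes three post-baseline assessments. The comparison is described in one sentence: "The score will be calculated and compared within group and between groups before and after medication".

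The Statistical analysis section names one method: "Paired-T test will be derived for statistically analysis". It states no significance level. The Participants section gives the size: "Sixty patients will be recruited for the study and divided into an intervention group and a placebo group".

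Two other places bear on the visits. The Intervention section says that after four weeks of dosing "the patients will stop taking SMS and placebo for another four weeks and then come back to OPD for clinical evaluation", so week 8 is an off-treatment assessment. The abstract, after listing the questionnaire and the other measurements, says "These data were collected at baseline, two weeks and four weeks after receiving medication" and does not mention week 8.

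**The concern.** A primary outcome should tell the reader which number decides the trial. Here three things are left open together:

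- **Score.** The instrument is assessed on several dimensions, and none is put first.
- **Visit.** Weeks 2, 4 and 8 are unranked. Weeks 4 and 8 answer different questions: effect at the end of dosing, and what remains four weeks later.
- **Contrast.** Within-group and between-group comparisons stand side by side. The only test named suits the within-group one.

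If the choice is made after the data are seen, the nominal error rate of any single test no longer describes the trial, and a reader cannot tell a true effect from selection. The within-group comparison adds a separate problem: it does not use the placebo arm, so it can be significant through change that both arms share.

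**Working it through.** **The plan's own figure.** The only design figure is the total of 60. It comes without level, power, effect size or standard deviation, so it cannot be reproduced, and no error rate is stated to check against.

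**Inputs from the document:** three post-baseline visits (Primary outcome), two in the abstract; both within-group and between-group comparisons (Primary outcome); 60 patients in two groups (Participants).

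**Assumptions:** two-sided 5% per test; 30 per arm, since no allocation ratio is stated; number of scores tested, k, taken as 1, 5 or 15, since the document gives no count; correlations as shown below.

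**Step 1. Between-arm tests at three visits, independent.** Chance of at least one false positive = 1 − 0.95^(3k).

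- k = 1: 1 − 0.95^3 = 14.3%
- k = 5: 1 − 0.95^15 = 53.7%
- k = 15: 1 − 0.95^45 = 90.1%

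For positively correlated tests these serve as upper reference values.

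**Step 2. Allowing for correlation.** Simulation of normal test statistics under no treatment effect (100,000 draws), with equal correlation between scales and equal correlation between visits:

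| Scores k | Independent | Correlations 0.5 and 0.5 | Correlations 0.7 and 0.7 |
|---|---|---|---|
| 1 (visits only) | 14.3% | about 12% | about 11% |
| 5 | 53.7% | about 41% | about 30% |
| 15 | 90.1% | about 69% | about 48% |

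A second simulation used t-tests on change from baseline, with 30 per arm, correlation 0.5 between visits and 0.3 to 0.7 between scales (4,000 runs per scenario). It gave about 12-13% for one score, 33-46% for 5 scales and 55-80% for 15, which is consistent with the table.

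**Step 3. Adding within-arm tests.** Counting paired tests in the SMS arm as well, the second simulation gave about 19-21% for one score, 49-64% for 5 scales and 73-94% for 15.

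**Step 4. Change shared by both arms.** Step 3 assumes that neither arm changes over time. Suppose instead that both arms improve by the same amount d, in standard deviations of change, with no treatment effect. The paired t-test in the SMS arm then follows a noncentral t distribution with 29 degrees of freedom and noncentrality d√30.

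- d = 0.3: noncentrality 0.3 × 5.477 = 1.64; significant improvement in about 36% of trials
- d = 0.5: noncentrality 0.5 × 5.477 = 2.74; significant improvement in about 75% of trials

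This is at one visit on one score, so correcting for the number of tests would not cure it.

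**Step 5. The abstract's visit list.** With two post-baseline visits and independent between-arm tests, 1 − 0.95^(2k) gives 9.8% for k = 1, 40.1% for k = 5 and 78.5% for k = 15. The result is lower but still above 5%.

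**Step 6. With one pre-specified between-arm comparison** the rate returns to 5%. Keeping every between-arm test under Bonferroni would require 0.05/3 = 0.0167 per test for one score, 0.05/15 = 0.0033 for 5 scales and 0.05/45 = 0.0011 for 15.

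**The case against.** The strongest reply has four parts.

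1. **One score may be meant.** The comparison sentence speaks of the score in the singular. This stands as a possible reading, and it is why k = 1 is in the table. It sits badly with an outcome assessed on several dimensions, the score is still not named, and three visits alone take the rate to about 11-14%.

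2. **The natural visit is week 4.** Baseline against end of dosing is a fair reading of before and after medication, and the abstract's list ends there. The text does not say so, however, and the Primary outcome section includes week 8 on the same footing as the other visits.

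3. **Multiplicity rules belong in an analysis plan that is not shown.** This is right as far as procedures go, and their absence is not the complaint. Defining the primary outcome is a protocol task. The article has a section for it, and that section sets several dimensions, three visits and two kinds of comparison without ranking them.

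4. **The size rests on assumptions.** It does. A reader might infer that a chance positive is likely, or that any one significant scale at any visit would count as success. The document supports neither. It gives no scale count, level or success rule, and at correlations of 0.7 the between-arm figure stays below one half even with 15 scales.

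A reader might also infer that the laboratory values are a further primary endpoint, because they are described under the same heading. The text gives them a role in general health status and safety, so their placement is an editorial matter.

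**Conclusion.** The point holds in this form: the Primary outcome section does not say which QLQ-C30 score, visit or contrast decides the trial, nothing elsewhere in the article does, and the visit lists in the abstract and the main text disagree. The error rate exceeds 5% under every reading that tests three visits between arms. The excess is moderate if one score is meant (about two to three times nominal) and large if many scales are tested. How large cannot be settled from the document.

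Confidence is high that the deciding comparison is not named, and lower for any particular percentage. The placement of within-group comparisons beside between-group ones is as serious as the count of tests, because it lets shared change be read as efficacy. This should be put right before unblinding.

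**What to change.** - **Primary outcome section:** name one endpoint, a between-arm contrast of one QLQ-C30 score at one visit. An example is change in global health status from baseline to week 4, the end of dosing. The choice of score is the sponsor's. Fatigue could be justified instead, since much of the rationale in the article concerns it.
- **Statistical analysis section:** replace the paired t-test, for this endpoint, with a test that compares two independent arms, such as ANCOVA adjusted for baseline or a two-sample t-test on change. Without this the new primary contrast would have no valid test.
- **Everything else:** label the other scales, the other visits and all within-arm changes as secondary or exploratory, with no efficacy claim resting on them.
- **Visits:** reconcile the list in the abstract with the one in the Primary outcome section.

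The cost is wording in these sections, with no change to visits or data collected. The one real loss is that a positive result on another scale or visit can no longer carry the conclusion. The Trial status section reports 36 patients recruited at submission of the manuscript. Current status is not known from the document, so the change should be dated and made before any unblinding.

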### Data collection

We will collect basic data such as gender, age, cancer type, stage, and metastasis or no metastasis at base line. Other than the basic data, such as gender and age, laboratory data, for example, WBC, Hb, Hct, CEA, platelet and HRV will be collected. GOT, GPT, BUN, and creatinine will also be recorded to facilitate the evaluation of liver and renal functions.

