All ingredients of SMS are considered to improve side-effects induced by chemotherapy or radiotherapy, as described above under TCM theory. In addition to the described effects of every ingredient of SMS, the formula also has a synergic effect not yet realized. Many studies have shown that TCM formulae exhibit more significant synergistic effects than all the ingredients combined [27,28]. Moreover, the safety of concentrated herbal extracts is also important in this study. Many studies have shown that herbs may cause liver or renal damage [29,30]. The concentrated herbal extracts used in this study are produced by a GMP pharmaceutical company in Taiwan. Due to the strict flow control during the manufacturing process, the concentrated herbal extracts are highly homogeneous with good quality control, which is very different from those obtained using traditional methods. Therefore, the concentrated herbal extracts are considered safer than the traditional herbs.

More efforts will be exerted to prove the efficacy of TCM in helping patients with cancer through ongoing studies. Future researchers will focus on finding effective TCM formulae to help patients ease the side effects of chemotherapy and radiotherapy.

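### The paired t-test, the only analysis named, is a poor safety analysis for GOT, GPT, BUN and creatinine: it usually misses marked rises in one to three of about 30 patients

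*Protocol article*

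**What the plan says.** - **Aim.** The Primary outcome section says the laboratory data will be used to "monitor the liver and renal functions to assess the safety of SMS". The Data collection section names the variables: "GOT, GPT, BUN, and creatinine will also be recorded to facilitate the evaluation of liver and renal functions".
- **Recognised hazard.** The Discussion treats the safety of the extract as important and states: "Many studies have shown that herbs may cause liver or renal damage".
- **Analysis.** The Statistical analysis section gives one method and attaches it to no outcome: "Paired-T test will be derived for statistically analysis". The Abstract (Methods/design) lists the recorded data, including GOT, GPT, BUN and creatinine, and gives their timing: "These data were collected at baseline, two weeks and four weeks after receiving medication". It then closes with "Paired-T test was used for statistical analysis".
- **Between-arm comparison.** The Primary outcome section states one for the QLQ-C30 score only. None is stated for the laboratory values.
- **Size.** "Sixty patients will be recruited for the study and divided into an intervention group and a placebo group". The allocation ratio is not given.

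**The concern.** Herb-related liver or kidney injury is an event in individual patients, usually few of them. A paired t-test asks whether the mean change in an arm differs from zero. A large rise in a few patients raises the standard deviation along with the mean, so the test statistic stays small even when those rises are clinically obvious.

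There is also a problem of attribution. Every participant is on chemotherapy or radiotherapy, so a before-after change within the SMS arm mixes any SMS effect with the effect of that treatment. The within-arm test can miss real injury, and it can also flag a shift that has nothing to do with SMS.

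What is at stake is the safety statement. If it leaned on this test, a few patients with marked rises could sit behind a non-significant p-value.

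**Working it through.** **Inputs.** From the article: 60 patients in two groups; paired t-test; GOT, GPT, BUN and creatinine as the liver and renal measures. Assumed, because the article does not give them: 30 per arm, two-sided 5% level, and every baseline value, SD and size of rise below. The article states no figure for safety, so there is none to reproduce.

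**Step 1. Noise-free case.** Let k of n patients rise by the same amount Δ and the others not change.

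- Mean change = kΔ/n
- Sample variance = Δ²·k(n − k)/[n(n − 1)]
- t = mean/(SD/√n) = √[k(n − 1)/(n − k)]

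Δ cancels. With n = 30, t = √[29k/(30 − k)], to be compared with 2.045 (29 degrees of freedom).

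| k of 30 | t | p |
|---|---|---|
| 1 | √(29/29) = 1.00 | 0.33 |
| 2 | √(58/28) = 1.44 | 0.16 |
| 3 | √(87/27) = 1.80 | 0.083 |
| 4 | √(116/26) = 2.11 | 0.043 |
| 5 | √(145/25) = 2.41 | 0.023 |

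Identical rises in up to three of 30 patients (10%) do not reach significance here, however large they are. Four do.

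**Step 2. With noise.** Simulation of 20,000 trials per scenario, with a baseline of 25 U/L, an SD of change of 5, 10 or 15 U/L, and k patients rising to 3, 5 or 10 times baseline (by 50, 100 or 225 U/L). The result depends on the ratio of rise to SD, which runs from 50/15 = 3.3 to 225/5 = 45. The entries are the range over all scenarios of the probability of a significant increase.

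| k of 30 | Paired t, SMS arm | Welch t on change, against an unaffected arm |
|---|---|---|
| 1 | 0–5% | 0–5% |
| 2 | 0–9% | 0–9% |
| 3 | 0–18% | 1–18% |
| 4 | 26–82% | 20–74% |
| 5 | 41–100% | 30–100% |

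With nobody affected, the same upper-tail rate is about 2.5%. A between-arm test on means does little better than the paired test, so the weakness lies in testing means and not only in the pairing.

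**Step 3. Attribution.** Suppose both arms drift by a common amount because of chemotherapy or radiotherapy, with no SMS effect. The chance that the paired test in one arm (n = 30) is significantly positive is 18%, 56% and 75% for an assumed drift of 0.2, 0.4 and 0.5 SD.

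**Step 4. What per-patient counting gives.** With 30 in an arm, the chance of seeing at least one case is 1 − (1 − risk)³⁰: 46%, 79% and 96% at true risks of 2%, 5% and 10%. With 0 of 30 observed, the two-sided 95% upper limit is 1 − 0.025^(1/30) = 11.6%. Fisher's exact test on counts is itself weak: p = 0.24 for 3 v 0, 0.052 for 5 v 0 and 0.024 for 6 v 0. The gain is that cases become visible by arm, with an interval that shows how little 30 patients can exclude. Another p-value would not add much.

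**The case against.** The strongest reply is that the article never ties the paired t-test to safety. The Statistical analysis section attaches it to no outcome. The Primary outcome section speaks of monitoring, and under Intervention "patients will come back to out-patient-department (OPD) for clinical evaluation and medication" at two and four weeks, which is compatible with review of each patient's results. Toxicity grades, shift tables and adverse-event rules are commonly left to a full protocol or analysis plan, neither of which is shown.

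Much of this stands. A reader might infer that safety rests on the paired t-test alone, or that a non-significant result will be reported as proof of safety. The documents support neither: no decision rule is stated, and individual review is not excluded. The absence of grading or adverse-event detail is no finding.

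A reader might also infer that a test on means cannot detect such injury at all, or that more severe injury always lowers the chance of detection. Neither holds. At four or five of 30 the test often detects it, and at four affected detection rises with severity. With an assumed SD of 60 U/L and rises of 150 or 270 U/L, detection increases with severity even at two affected (7.8% to 8.6%) and three (13% to 17%), although it stays low.

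The placebo arm is also available, and a between-arm look at the laboratory values is not ruled out; it is simply not stated.

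What the reply does not remove is that a method is named, without restriction, as the only analysis, and that the Abstract places it after a list containing the four safety values. That is a stated method unsuited to a stated aim, which is more than silence.

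**Conclusion.** The point holds in limited form. On the natural reading the paired t-test covers GOT, GPT, BUN and creatinine. Applied to them, it usually misses marked rises in one to three of about 30 patients: t is 1.00 to 1.80 without noise, and simulated detection is roughly 0 to 18%. It becomes sensitive only at about four or five of 30. It also cannot separate SMS from concurrent cancer treatment. A non-significant result could therefore be falsely reassuring; the article does not say it would be used that way.

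The noise-free result needs only 30 patients in the arm and equal rises among those affected. The simulated ranges rest on assumed SDs and rises, none of which are in the article.

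**What to change.** In the Statistical analysis section, say which outcomes the paired t-test is for, and leave the safety laboratory values out of that list.

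In the Primary outcome section, where safety is described, state that GOT, GPT, BUN and creatinine will be summarised per patient by arm: worst post-baseline value against baseline, by a standard grade that the sponsor chooses before unblinding. Report the number and percentage of patients who worsen in each arm, and the between-arm difference with an exact confidence interval. Add that a non-significant test is not evidence of safety.

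The cost is wording and one table from data already being collected, with no new visits or patients. Recruitment stood at 36 of 60 when the article was submitted, so at that stage the change could still be made before unblinding. The downside is a more modest safety statement: intervals will be wide (0 of 30 still leaves an upper limit of about 11.6%), and counts have little power for a formal test.

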## Discussion

There is an ever increasing number of patients suffering from cancer every year. Although various types of treatment are performed on a routine basis, surgery, chemotherapy and radiotherapy remain the major modes of cancer treatment. Through chemotherapy or radiotherapy, not only tumor cells, but also normal cells, are simultaneously killed. Many side effects, such as lower white blood cell count, general weakness and loss of appetite are often observed during and after the treatment. These side effects may lower the quality of life of these patients.

Many CAMs show significant improvements in chemotherapy- or radiotherapy-related side effects and TCM is the most common means of CAM in Taiwan. One study reported utilizing TCM to improve the quality of life in women undergoing chemotherapy for ovarian cancer and the result showed no significant difference in global health status but there was less neutropenia [13]. Another study used TCM for patients with colon or breast cancer requiring chemotherapy; there was no significant difference in hematologic toxicity but there was a significant impact on the control of nausea [20]. We think that we can select formulae according to the most common symptoms of the patients using TCM theory and lessen the side effects caused by chemotherapy in cancer treatment.

SMS is used for the treatment of myocardial infarction (MI) and has a protective effect for renal ischemic damage during MI [19,21]. Some studies also reported that SMS can improve sperm viability and sperm movement parameters *in vitro*[22]. According to ancient TCM theory, SMS could also prevent fatigue in the general population and especially when used in patients with qi and yin deficiency. It is composed of processed *G. radis, L. spicata, and S. fructus*. Ginseng was reported to have some activity and tolerable toxicity to cancer-related fatigue [23]. Ginseng polysaccharides also had anti-fatigue activity in a study in mice [24]. *L. spicata* was used for yin deficiency according to TCM theory and had hypoglycemic and hypolipidemic potential for type 2 diabetes[25]. *S. fructus* was used for the benefit of qi and promoted body fluid production according to TCM theory and was also reported to have effects in viral- and chemical-induced hepatitis [26].

All ingredients of SMS are considered to improve side-effects induced by chemotherapy or radiotherapy, as described above under TCM theory. In addition to the described effects of every ingredient of SMS, the formula also has a synergic effect not yet realized. Many studies have shown that TCM formulae exhibit more significant synergistic effects than all the ingredients combined [27,28]. Moreover, the safety of concentrated herbal extracts is also important in this study. Many studies have shown that herbs may cause liver or renal damage [29,30]. The concentrated herbal extracts used in this study are produced by a GMP pharmaceutical company in Taiwan. Due to the strict flow control during the manufacturing process, the concentrated herbal extracts are highly homogeneous with good quality control, which is very different from those obtained using traditional methods. Therefore, the concentrated herbal extracts are considered safer than the traditional herbs.

More efforts will be exerted to prove the efficacy of TCM in helping patients with cancer through ongoing studies. Future researchers will focus on finding effective TCM formulae to help patients ease the side effects of chemotherapy and radiotherapy.

